## Background

### Background and rationale

Ankle fractures are extremely common, accounting for over 20% of all lower-limb fractures [1] . The AO (Arbeitsgemeinschaft für Osteosynthesefragen) system of open reduction and internal fixation (ORIF) technique, has become the accepted treatment for unstable ankle fractures [2]. The traditional post-surgery management has been based on 6 weeks’ non-weight-bearing, with the ankle immobilised in a below-knee cast.

Detrimental sequelae of this traditional regimen are a combination of joint stiffness, reduced range of motion (ROM), pain, reduced circulation, oedema and muscle atrophy [3–6]. This presentation has been termed ‘fracture disease’ [2, 7, 8] and ‘cast disease’ [7, 9–12]; the term ‘cast disease’ is used through the remainder of this protocol. Attempts to address cast disease can necessitate extended rehabilitation, but even so, not all patients obtain the desired recovery [13]. The necessity of delaying rehabilitation for 6 weeks is being increasingly questioned.

Systematic reviews of previous randomised control trials (RCTs) conclude that early rehabilitation is safe, citing no statistical difference between early rehabilitation and control groups in terms of fixation failure, delayed and non-union and rates of infections. [13–20]. An exception has been where rehabilitation was started immediately after surgery [21], yielding an unacceptable wound infection rate of 66%, in comparison to 16% in the control group. In contrast, delaying rehabilitation until at least 10 days post surgery resulted in a wound infection rate of just 9% [22].

While timing appears to be the single biggest risk factor for iatrogenic wound infections, the reviews identify ambiguity surrounding the evidence supporting effectiveness of early rehabilitation due to risk of methodological bias. For example, underpowered sample sizes and inadequacies in reporting of interventions and results [13–20]. The Cochrane reviewers concluded that while early rehabilitation is mostly safe, there is only ‘limited evidence’ on its effectiveness [13].

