#### Exclusion criteria

Inability to provide informed consent, or declining participationComorbidities: diabetes requiring prescription drugs, non-healing leg/foot ulcers, oral or intravenously administered steroid users, pre-existing ankle arthritis and concurrent or history of significant ipsilateral or contralateral lower limb injury/condition, e.g. prosthesis in lower-limb joints, or neurological disordersAt the 2-week clinic visit a patient may be excluded if, based on individual clinical decision, there is notable risk that early wound movement will impede satisfactory healing.Those unable to commit to weekly clinic visits, if assigned to the EMADE intervention group

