### Interventions

Pre-operatively and, during the first two post-operative weeks, participants receive identical care consisting of admission to hospital and consultant supervised surgery including management on a standard care pathway. Participants are discharged home in a cast and reviewed 2 weeks following surgery. All participants undergo x-ray post surgery and wound inspection following cast removal during the 2-week review (10 to 19 days post surgery). All participants are non-weight-bearing throughout the study until the 6-week point.

The EMADE intervention is a progressive home exercise programme that includes range-of-motion (ROM) and strengthening exercises, and is conducted by the participant up to six times a day. To be able to conduct the exercises, at the 2-week fracture clinic review, those in the EMADE intervention group are fitted with a removable below-knee cast with Velcro retaining straps.

The EMADE programme starts with light intensity and low daily repetitions, and as the weeks progress, becomes progressively more intensive and repetitive. For example, exercises start resistance-free, and are followed by elastic-exercise-band resistance; while the daily repetitions start twice daily and build up to six times daily. These progressions are taught during weekly face-to-face sessions between the week-2 and week-6 fracture clinic reviews.

During the physiotherapy sessions, participants receive manual therapy consisting of 5 to 10 min of joint and soft-tissue manipulation to the ankle complex. Advice and education is on-going and includes; healing processes, control of pain and swelling, and expectations of fluctuation of pain and swelling. These sessions take part in the recruiting hospital, and are provided by an experienced physiotherapist trained in the application of the EMADE intervention.

To encourage compliance with the EMADE home exercise programme, participants are provided with written and pictorial exercise sheets. These were developed through patient input and include diary sheets, although completion of the diary sheets is neither mandatory nor used in data collection. Participants are not paid to attend, but a basic travel allowance is offered to attend the additional sessions for the study, but not for usual NHS care. Participants in the usual care group are treated in a below-knee cast and remain non-weight-bearing until the 6-week point.

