Adjustment for baseline scores, through analysis of covariance, will be conducted for OMAS, EQ-5D-5 L and A-FORM and compared with unadjusted scores. Impact of covariates will be further explored through regression analysis. Initial analysis for co-variates where significance is nearly reached (*p* > 0.10) will be taken forward into a statistical model. Due to the bimodal impact of age and sex, these will be included in this analysis. Other exploratory analysis for potential covariates may include impact of smoking, previous level of physical activity, type of fracture (AO classification), complexity of surgical repair and any subsequent removal of metal work; most notably removal of syndesmosis screw(s) for which stratification was applied at randomisation. Analysis will also be conducted using modified ITT by excluding those participants who attend only one session or less of EMADE sessions.

Sub-groups will include return to work for those unable to work due to their ankle fracture at the time of randomisation, and similarly, return to driving for those unable to drive due to their ankle fracture at the time of randomisation. Frequency of complications will be described but, based on the published literature, it is anticipated that frequency will be sufficiently low not to warrant statistical analysis.

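### Complications are expected to be too rare to analyse, yet the only rate cited at EMADE's timing is 9% wound infection; report a between-arm risk difference with a 95% CI

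*Protocol article*

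**What the plan says.** The Protocol article, Data processing, gives both a rule and its reason. The rule is that complications are only to be described. The reason, drawn from earlier publications, is that "it is anticipated that frequency will be sufficiently low not to warrant statistical analysis". No rate or expected count is attached to that statement.

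The only complication rates in the article are the wound-infection rates in Background and rationale:

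- For a trial that began rehabilitation immediately after surgery, described as an exception: "yielding an unacceptable wound infection rate of 66%, in comparison to 16% in the control group".
- For a later start: "delaying rehabilitation until at least 10 days post surgery resulted in a wound infection rate of just 9" per cent.

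The same section reports that systematic reviews judged early rehabilitation safe, "citing no statistical difference between early rehabilitation and control groups in terms of fixation failure, delayed and non-union and rates of infections", and names timing as apparently the largest single risk factor for wound infection caused by treatment.

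Under Interventions, all participants have an x-ray and "wound inspection following cast removal during the 2-week review (10 to 19 days post surgery"; EMADE begins from that visit. Under Exclusion criteria, a patient may be excluded at that visit if "there is notable risk that early wound movement will impede satisfactory healing".

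Elsewhere in Data processing, categorical data are to be given as frequencies and proportions and compared by chi-square or Fisher's exact test as indicated. Adverse events and x-ray findings are recorded (Secondary outcome measures).

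**The concern.** The reason for not analysing complications is an appeal to the literature. The one literature figure in the article that matches EMADE's start time is 9%, which is not obviously a rare event in a trial of this size. Low frequency is also a weak ground for setting aside the article's general rule for categorical data, since Fisher's exact test is meant for sparse tables.

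Wound infection is the harm that the Background itself ties to timing, and EMADE is a change in timing. If complications are only described arm by arm, the report will not say how large an excess of infections the data leave open. The Background criticises earlier trials for being underpowered while relying on reviews that found no statistical difference in harms. Reporting harms without an interval would leave this trial's readers in the same position.

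**Working it through.** **Inputs.** Sample size calculations: difference of 10 OMAS points, SD 19.5, 5% significance (two-sided assumed), 80% power, 120 participants before attrition, 156 to be randomised. Trial design: 1:1 allocation, hence 60 or 78 per arm. Background: 9% wound infection at a start of at least 10 days. Assumed by this review, not in the article: a lower rate of 2% to 5%.

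**The plan's own figure.** n per arm = 2 × (1.96 + 0.842)² × 19.5² / 10² = 59.7, so 60 per arm and 120 in total. This matches. The article states no expected number of complications, so there is nothing further to reproduce.

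**Expected wound infections, same rate p in both arms** (total = 2 × n per arm × p):

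| Rate | 60 per arm (N=120) | 78 per arm (N=156) |
|---|---|---|
| 9% (cited) | 120 × 0.09 = 10.8 | 156 × 0.09 = 14.0 |
| 5% (assumed) | 6.0 | 7.8 |
| 2% (assumed) | 2.4 | 3.1 |

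At 9%, the chance of seeing no infection in an arm of 60 is 0.91^60 = 0.3%. At 2% it is 0.98^60 = 30%.

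**Precision of the risk difference** (approximate 95% half-width = 1.96 × √(2p(1−p)/n)):

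- 9%, n = 78: 1.96 × √(2 × 0.09 × 0.91 / 78) = 9.0 points.
- 9%, n = 60: 1.96 × √(2 × 0.09 × 0.91 / 60) = 10.2 points.

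The Newcombe interval, which suits small counts better, is slightly wider: 7/78 against 7/78 gives about ±9.6 points. Equal observed rates near 9% would therefore leave open an excess of about 9 to 10 points, roughly a doubling.

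**Would a significance test help?** As an illustration only, take 9% against 16%. Power is 21% (normal approximation) or 14% (Fisher) at 60 per arm, and 26% or 20% at 78 per arm; 80% power would need 350 per arm. A non-significant result would say very little, so the useful quantity is the interval.

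**The case against.** The strongest defence is that 9% need not carry over. The trial excludes drug-treated diabetes, oral or intravenous steroid use and non-healing ulcers. It allows exclusion at the 2-week visit on wound grounds, and it randomises only after baseline measures at that visit, so infections evident earlier precede randomisation. The article does not show which population the 9% came from or when counting began. This stands: at 2% to 5%, description alone is easier to defend. But the article states no such lower rate, and an interval can be computed at any count.

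Second, complications is a wider term than infection, and no rate is quoted for fixation failure or non-union. So the tension with the Background is shown for wound infection only.

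Third, with so little power, declining to test is reasonable. That is accepted; it argues for an interval in place of a test, not for having neither.

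Fourth, table formats are commonly left to an SAP. Here, though, the article itself states the choice and gives its reason.

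Some stronger readings are tempting, and the article does not support them:

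- That infection rates of 16% or 66% are to be expected. The 66% followed an immediate start, which the article calls an exception, and the 16% is that same trial's control arm. EMADE's whole window lies within the later-start category.
- That analysis is forbidden or only raw counts will appear. The wording is an expectation, and frequencies and proportions are planned.
- That the trial plans a formal safety conclusion. No objective concerns safety, and the adoption statement refers to clinical benefit and cost-effectiveness.

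**Conclusion.** The concern holds in a limited form. The low-frequency premise is given without a rate and sits poorly with the one figure the article cites at EMADE's timing. If 9% applied in both arms, the trial would see about 11 to 14 wound infections in total, and a risk difference could be estimated to within about 9 to 10 points (approximate half-width). If the exclusions bring the rate down to an assumed 2% to 5%, about 2 to 8 are expected and the premise is easier to accept. These figures assume outcomes known for all 120 or 156 participants; losses to follow-up would reduce the counts and widen the intervals.

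The primary OMAS analysis is unaffected. The change is worth making because it concerns the main harm that the article itself recognises and uses data already being recorded.

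**What to change.** Replace the sentence on complications in Data processing with one along these lines: *Wound infection, fixation failure or reoperation, and any complication will be reported by arm among all randomised participants as n (%), with the between-arm risk difference and its 95% confidence interval (Newcombe or exact). No reliance will be placed on a significance test, and absence of a significant difference will not be taken as evidence of safety.*

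If the low-frequency expectation is kept, state the rate it rests on and why that rate should be below the 9% cited in the Background.

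The cost is one sentence and one more table, with no new data collection. The downside is that the intervals will be visibly wide.

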### Health economics

Health economic evaluations will be conducted from a societal perspective and from the service commissioner’s perspective. The societal perspective will be limited to incremental cost-effectiveness ratio (ICER) of the natural units of; return to work and return to driving (sub-groups as described earlier). Based on the EQ-5D-5 L PROM data, a cost-utility analysis (costs per quality-adjusted life year; QALY) will be performed from the local commission’s perspective. Sensitivity analysis will include the variability of the additional EMADE physiotherapy service costs; for example, £18 to £25 per session (2016 rates) and frequency of post-6-week physiotherapy sessions. The final methods for health economic evaluations will be guided by discussion with a health economist.

### Governance

Governance procedures were developed following Good Clinical Practice (GCP) guidelines (non-CTIMP) [37] with agreements from the local sponsors and the Ethics Committee. This includes reporting procedures for adverse and serious adverse events. The governance procedures for this trial has been independently audited by the Quality Assurance and Good Clinical Practice Audit Office, Nottingham Health Science Partnership, with a favourable outcome.

Due to the size of the trial it was considered unnecessary to form a data monitoring committee. This study will comply with the requirements of the UK Data Protection Act 1998 with regards to the collection, storage, processing and disclosure of personal information and will uphold the Act’s core principles. Access to collated participant data will be restricted to the research study staff. Allocation of a unique code to each participant will help to ensure confidentiality and anonymity. These identifiers will be used in all data, study material and reporting. Published results will not contain any personal data that could allow identification of individual participants. All electronic data will be stored on host NHS and University computers, with limited access under username and password protection system, as per host NHS and University ICT policies. Paper-based data will be stored in a locked filing cabinet in a key-coded room.

### Ethics approval and amendments

NRES Committee East Midlands – Nottingham 2, reviewed and approved this study on 4 November 2014 (14/EM/1213). The Ethics Committee and sponsors have been informed of important protocol changes and events. Amendments have focussed on an embedded study, which has subsequently been removed from the trial; only two participants were recruited to this embedded study and both participants withdrew from the trial during their in-patient stay and did not reach randomisation. Other amendments include: (1) expanding the recruitment period from the in-patient period, up to and including the 2-week clinical visit and (2) reducing the burden on the participant by decreasing the number of PROMs and permitting PROM completion online. The time point of randomisation, the intervention, and the primary and core outcome measures, have all remained unchanged since the start of recruitment.

### Dissemination

Routes of dissemination will include:Medical and associated, conferences, meetings and journalsPatient participation seminars and meetings, such as those organised by Arthritis Research UKFurther data-sharing plans for the current study are unknown and will be made available at a later date

Decisions on authorship will be directed by guidelines from International Committee of Medical Journal Editors [38].

## Discussion

The aim of this trial is to determine if EMADE is more effective than usual care in reducing symptoms and restoring function in those who have undergone open reduction and internal fixation following a Weber B ankle fracture. While EMADE does not contain novel modalities, what is distinctive for this trial is EMADE’s early clinical application of a progressive ankle rehabilitation programme, being at 2 weeks post ankle surgery versus the traditional of starting after 6 weeks of immobilisation.

We do not anticipate significant bias from known confounders, such as age and sex, and unknown confounders, due to the limiting effect on bias from random allocation. However, as a pragmatic study, there is no control nor influence over the quality and volume of care, including physiotherapy, after the end of the intervention at 6 weeks post surgery.

While compliance with the EMADE home exercise programme will be encouraged through the weekly face-to-face reviews and the written and pictorial exercise sheets, compliance will still be a potential confounder. However, as a pragmatic trial, this level of encouragement and supervision was felt to be appropriate, as it reflects current physiotherapy clinical practice.

It may be argued that starting physiotherapy early with EMADE will reduce the number of sessions subsequently required and, thus, the overall number of sessions may not be significantly different from usual care. However, while this remains unproven it is pertinent to assume that EMADE is more expensive (approximately £54 to £75) and, therefore a cost-utility analysis in QALYs is required from the commissioner’s perspective to determine if EMADE is value for money. Also, while QALY units will be valued by commissioners, the use of natural units; return to driving and return to work will be tangible to patients and their families.

As this intervention requires no specialist equipment, it is suitable for provision in both primary and secondary care-based physiotherapy departments and, therefore, has potential for broad clinical impact. The trial design limits bias where possible, including during the collection, processing and analysis of PROM data. Objective outcomes will be recorded unblinded; however, being secondary outcomes and analysed separately from the PROM data, the potential impact of bias from objective data will have limited impact on the overall quality of the study.

The primary objective of this study is to test whether the EMADE intervention is effective in the clinical setting. Therefore, it is appropriate to assess effectiveness of EMADE against usual care in the clinical setting, through a p-RCT. If significant clinical benefits and cost-effectiveness are demonstrated, EMADE should become a viable treatment option. A larger-scale, multicentre trial may be required to influence national guidelines.

### Trial status

At the time of manuscript submission 111 participants had joined the trial.

### Protocol version

Version 2.2, 18 April 2017. First recruit June 2015, last expected mid 2018.

## Abbreviations

A-FORM: Ankle-Fracture Outcome of Rehabilitation
AO: Arbeitsgemeinschaft für Osteosynthesefragen
ARUK: Arthritis Research UK
CPAQ: Clinical Physical Activity Questionnaire
EMADE: Early motion and directed exercises
EQ-5D-5 L: EuroQol 5 Dimension 5-Level Questionnaire
ICER: Incremental cost-effectiveness ratio
OMAS: Olerud and Molander Ankle Score.
ORIF: Open reduction and internal fixation
p-RCT: Pragmatic randomised controlled trial
PROM: Patient-reported outcome measure
ROM: Range of motion
